###### Multivariate statistical analysis

2.9.3.2.4

Using MetaboAnalyst 4.0 software (http://www.metaboanalyst.ca), multivariate statistical analyses, such as principal component analysis (PCA), partial least squares discriminant analysis (PLS-DA), and orthogonal partial least squares discriminant analysis (OPLS-DA), were carried out on the obtained three-dimensional data matrices to perform differential metabolite analysis. PLS-DA and OPLS-DA are supervised data dimensionality reduction models. PCR is an unsupervised model that can compress the data into a few main variables to characterize the data. It is primarily used to observe the distribution of each group of samples in their natural state and the overall differences. The variable weight value (variable important in the projection, VIP) in the OPLS-DA model can be used to determine which metabolites are different between the two groups, and metabolites with VIP>1 are typically considered differential metabolites. Multidimensional statistical methods due to the simultaneous influence of correlation and intra-group and inter-group variance and other factors, sometimes the differentially expressed variables found may not be very significant differences in a single dimension, so it is also necessary to validate at the unidimensional statistical level (two-sided/test, p < 0.05) as a way to further screen metabolic markers. The relative contents of the various samples can be hierarchically clustered based on the differential metabolites tested in the samples; the outcomes are displayed as a heat map. Lastly, by comparing the serum relative content levels of the screened metabolic indicators with the study’s PSQI scale scores, including follow-up data, Spearman’s rank correlation analysis was carried out for each metabolic marker.

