**Methods:**

A single-center, double-blind, clinical trial was the study’s design. For this study, a total of 99 participants were enrolled, and they will be split into two groups: one for insomnia and the other for health. There are 33 healthy people in the healthy group and 66 insomnia patients in the insomnia group. Acupuncture treatment will be administered to the intervention group three times a week for four weeks, for a total of twelve treatments, and will be followed up for 3 months. A combination of UPLC-Q/TOF-MS and UPLC-QQQ-MS/MS was used to qualitatively and quantitatively examine the serum of 99 participants. The Pittsburgh Sleep Quality Index (PSQI) and serum metabolomics provided the primary findings. The Insomnia Severity Index (ISI), Hyperarousal Scale (HAS), Fatigue Feverity Scale (FSS), Hamilton Depression Scale (HAMD), Hamilton Anxiety Scale (HAMA), Sleep Diary and The Montreal Cognitive Assessment (MoCA) were the secondary outcomes. For the insomnia group, serum will be collected at baseline, at the end of treatment, and the scale will be collected at baseline, after 4 weeks of treatment, and at 3 months of follow-up. For the healthy group, serum will be collected at baseline.

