In order to investigate the pathophysiology of diseases and the mechanisms by which therapies work, metabolic technologies is used to identify the various changes that occur in biological systems under various medical conditions. It also facilitates the rapid and thorough analysis of differential metabolites to elucidate physiological or pathological pathways of metabolism (15). Additionally, the technology explores the relationship between pathophysiological changes and small molecule metabolites. 328 metabolites are thought to be very important in human sleep, and particularly abundant metabolites include carnitine, aromatic amino acids, phosphatidylcholine, and lysophosphatidylcholine (16).Previous studies have explored the unique serum metabolomic profile of insomnia and found that insomnia induces perturbations in metabolites of amino acid metabolism, neurotransmitter metabolism, and glycolipid metabolic pathways (17). One study showed that by collecting plasma from insomnia patients and applying untargeted metabolomics analysis, 64 metabolites were associated with sleep duration, and elevated levels of amino acid metabolites (such as branched-chain amino acids and gamma-glutamyl dipeptide) were associated with later sleep duration (18). In another study, elevated energy metabolites and reduced branched-chain amino acid catabolic metabolites, as well as altered glucose metabolism, were observed in patients with insomnia by comparing insomnia patients with healthy controls, suggesting an increased susceptibility to diabetes in insomnia patients (19). Insomnia leads to significant alterations in specific metabolic pathways, which may be evidence of a link between insomnia and other somatic and psychiatric disorders. Therefore, this study aims to utilize metabolomics techniques to qualitatively and quantitatively analyze the sera of healthy individuals and patients with insomnia, in order to screen for differential metabolites, further explore the possible pathogenesis of insomnia, and search for objective biomarkers for it.

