### Study design

2.1

The study design is a single-center, double-blind, clinical trial to investigate the metabolic pathways and possible mechanisms underlying the efficacy response of electroacupuncture for insomnia. The study protocol follows the SPIRIT guidelines, 99 subjects will be recruited and divided into an insomnia group and a healthy group. The International Classification of Sleep Disorders, Third Edition (ICSD-3) diagnostic criteria will be used to diagnose subjects with insomnia. Those who meet the inclusion criteria will also sign an informed consent form, complete the following scale assessments, and have their serum collected: PSQI and ISI to measure sleep; HAS to measure hyperarousal state; HAMD and HAMA to measure mental state; and FSS to measure physical and mental fatigue, sleep diary to measure sleep behavior, and MoCA to measure cognition to gather baseline assessment data. This will be followed by 4 weeks of treatment. Retesting of the above scales will be completed at the end of treatment and at 3 months follow-up, as well as serum collection’s will be completed at the end of treatment. The healthy group will complete serum collection at enrollment. The insomnia group will be randomly divided into Group A and Group B, matched with the healthy group. Group A and the healthy group will be screened for differential metabolites using metabolomics analysis with non-targeted UPLC-Q/TOF-MS, and Group B will be quantified for the screened differential metabolites using metabolomics with targeted UPLC-QQQ-MS/MS. The flow chart of the experiment is shown in **Figure 1**. The flow schedule is shown in **Figure 2**.

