###### Mass spectrometry conditions

2.9.3.1.2

the electrospray ionization (ESI) source was used to collect data in positive and negative ion modes; the parameters of the TOF-MS scanning mode were set as follows: relative molecular mass (RMM) scanning range of m/z50~1,000; accumulation time of 0.1500 s; ionization temperature (TEM) of 550 °C; nebulization gas (GS1) of 55 psi; auxiliary heated gas (GS2) of 55 psi; curtain gas (CUR) of 30 psi; de-clustering voltage (DP) 80 V; collision energy (CE) 5 eV; spray voltage (ISVF) in positive and negative ion modes were 5500, 4500 V. Data-dependent scanning (IDA), intelligent dynamic background subtraction (DBS), and high-sensitivity mass spectrometry data acquisition modes were used. The relative molecular mass (RMM) scanning range of the ion scanning mode was m/z50~1,000; the collision energy was (30 ± 15) ev, and the other main parameters were the same as those of the TOF-MS mode.

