### Statistical analysis

2.13

In this study, the software SPSS25.0 was first used to process the experimental data, and the measurement data were expressed by `x ± s, and the count data were expressed by the rate or the constitutive ratio. Comparison of the measurement data between the two groups was firstly analyzed by normality analysis, a t-test was used for the measurement data that conformed to normality and chi-square, and a non-parametric rank-sum test was used for the measurement data that did not conform to the normal distribution; chi-square or Fisher’s exact probability method was used for the count data. p<0.01 was taken as the difference was significant; p<0.05 was taken as the difference was statistically significant between the two groups.

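### Differential metabolites, a primary outcome, are selected at VIP>1 plus a per-metabolite p<0.05 with no error control across an untargeted panel

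*Protocol article*

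**What the plan says.** The abstract names two primary outcomes: "The Pittsburgh Sleep Quality Index (PSQI) and serum metabolomics provided the primary findings". Under Study design (2.1), "Group A and the healthy group will be screened for differential metabolites using metabolomics analysis with non-targeted UPLC-Q/TOF-MS". The Mass spectrometry conditions for that platform (2.9.3.1.2) use the source to "collect data in positive and negative ion modes", over m/z 50 to 1,000. The number of features that will enter the analysis is not stated.

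The selection rule is in Multivariate statistical analysis (2.9.3.2.4). First, "metabolites with VIP>1 are typically considered differential metabolites". Then a univariate step follows: "it is also necessary to validate at the unidimensional statistical level (two-sided/test, p < 0.05) as a way to further screen metabolic markers". The same section goes on to Spearman correlations of each marker with PSQI, and Metabolic pathway analysis (2.9.3.2.5) adds KEGG-based enrichment. The general rule in Statistical analysis (2.13) is again that "p<0.05 was taken as the difference was statistically significant between the two groups". None of these sections names a false discovery rate, a q-value or a family-wise correction.

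There is a second stage. Study design and the Discussion say that the screened metabolites will be quantified in Group B on a targeted platform, and the Discussion presents this as validation of the screen. Neither place gives a criterion for a metabolite to count as validated, or says clearly what Group B is compared with.

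**The concern.** The two filters look like a double safeguard, with the univariate test checking the multivariate one. Both are computed on the same samples and measure nearly the same thing, so the second is not independent validation of the first. A per-feature 5% level over a panel of unknown but probably large size yields a marker list even when insomnia has no metabolic signature.

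The list has several uses. It decides which metabolites are quantified in Group B, and it supplies the enrichment analysis and the PSQI correlations. The Discussion also plans to read a reversal of these abnormalities after treatment as proof of mechanism. A metabolite selected because Group A happened to be extreme at baseline will tend to move back on re-measurement, to the extent that the chance difference reflects assay or day-to-day variation. A false marker can therefore resemble a reversal.

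**Working it through.** **The plan's own figures.** The article gives no feature count, false-marker count or error rate for metabolomics, so there is nothing to reproduce on this point. Its one calculation, 52 and 26 participants for PSQI at effect size 0.8, does reproduce (exact t-test power 0.908) but does not concern the metabolite screen.

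**Inputs.** Two-sided level 0.05 per metabolite and VIP>1 (2.9.3.2.4). The number of features, m, is not stated, so 100 to 5,000 is assumed. The figure 328 is background from the Introduction ("328 metabolites are thought to be very important in human sleep") and is not this trial's panel. Group A is 33 if 66 patients are split 1:1, or about 17 if the 33 named in Randomization (2.5) are split. The healthy group is 33.

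**Step 1: expected false markers if nothing differs.** E = 0.05 × m.

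| Features tested (assumed) | Expected to pass p<0.05 |
|---|---|
| 100 | 5 |
| 328 | 16.4 |
| 500 | 25 |
| 1,000 | 50 |
| 5,000 | 250 |

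With independent tests the chance of at least one is 1 − 0.95^100 = 0.994 at m = 100, and effectively 1 from m = 328.

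**Step 2: does VIP>1 reduce this?** With one predictive component, VIP = √m × |w|, where w is the feature's weight and the squared weights sum to 1. Squared VIPs therefore average 1. Under the null with unit-variance scaling, VIP>1 corresponds roughly to |t|>1, which about 32% of noise features meet. A p-value below 0.05 needs |t| of about 2, so those features have already passed VIP>1.

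Simulation under the null (300 runs per setting, one predictive and one orthogonal component, unit-variance scaling, 33 v 33, independent features):

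| m | p<0.05 | p<0.05 and VIP>1 | Benjamini-Hochberg 5% |
|---|---|---|---|
| 328 | 16.1 | 16.1 | 0.06 |
| 1,000 | 50.2 | 50.2 | 0.06 |
| 2,000 | 100.5 | 100.5 | 0.05 |

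With 17 v 33, or with features correlated at 0.5 in blocks of 10, the means hardly change. Correlation widens the spread (SD 6.6 to 10.4 at m = 1,000, 33 v 33). Across all settings Benjamini-Hochberg gave a mean of 0.04 to 0.08 false markers.

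**Step 3: where VIP does help.** For m = 1,000, 33 v 33, 200 runs, log-normal feature SDs (assumed):

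- Pareto scaling, no true signal: false markers fall from 50 to about 44.
- Pareto scaling, 20% true features at d = 0.8: from 40 to about 21.
- Unit-variance scaling, 20% true features at d = 1.2: from 40 to 28.

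The article does not state the scaling.

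**Step 4: what Group B could remove.** Suppose the targeted stage required a same-direction p<0.05. With an independent comparator a false marker passes 2.5% of the time: 50 × 0.025 = 1.25, so about 1 of 50 remains. If Group B is compared with the same healthy sera, the two contrasts correlate at 0.5 (equal group sizes) and about 18% pass: 50 × 0.185 ≈ 9. The trial has only one healthy group.

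**The case against.** The strongest defence is that this is a first-stage screen. Different patients on a different platform follow, and a liberal screen with strict confirmation is a legitimate design. Strict control at the screen also costs power that Group B cannot recover. In simulation with 1,000 features, 5% of them true at d = 0.8, p<0.05 keeps 89% of true markers and q<0.05 keeps 46%; at d = 0.5 the figures are 51% and 3%. This stands as a reason to let a longer candidate list go forward. It does not rescue the rule as written, because the confirmation has no pass criterion and the downstream claims do not depend on it.

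A reader might infer four stronger points that the article does not support.

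- **Dozens of false markers.** That needs at least 480 tested features (480 × 0.05 = 24), a count given nowhere. Database matching (2.9.3.2.5) also means that raw features are not the same as named metabolites.
- **VIP>1 never protects.** Step 3 shows that this depends on scaling and on how much true signal there is.
- **The targeted stage only pursues noise.** It is described as validation and could remove most false markers.
- **A permutation or cross-validation check is wrongly absent.** A condensed article may leave that to the analysis plan.

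That the p-value is unadjusted is itself read from silence. Here, though, the silence surrounds a numeric cut-off that an analyst would apply literally.

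**Conclusion.** The point holds in limited form. The article fixes a selection rule for a primary outcome that passes about 5% of null features, whatever the panel size. The absolute number depends on the assumed panel: about 5 at 100 features to 250 at 5,000. VIP>1 does not change this under the null with unit-variance scaling, and reduces it only partly in the other settings tried. The Group B stage lessens the problem but, as described, cannot be relied on to control it. Because the threshold is written into the protocol, this is a badly fixed criterion and not a detail left to the analysis plan.

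**What to change.** In Multivariate statistical analysis (2.9.3.2.4):

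- Declare a metabolite differential, and carry it into pathway and PSQI correlation claims, only if its Benjamini-Hochberg q is below 0.05 over all tested features. Do this separately for Group A against healthy and for pre against post.
- If a more liberal list goes to the targeted assay, call its members candidates. Name the Group B comparator, and require same-direction, multiplicity-adjusted confirmation before any marker claim.
- Apply false discovery rate control to the enrichment and correlation tests.
- Use VIP for ranking only.

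This needs a few lines of analysis and protocol wording, and no new samples. The price is a shorter declared list and the loss of some true markers of moderate effect at the screen, which the candidate route to Group B mitigates.

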### Sample size

2.3

PASS 15.0 software was used to determine the sample size based on the nature of the study, with the control group being the healthy group and the treatment group being the insomnia group. Patients with insomnia use the PSQI score as an observed outcome indicator. Based on the pre-test results and literature review, the mean PSQI score for the drug control group is 10.76 ± 3.32 points, and it is anticipated that this score will decrease by 2.63 points for the insomnia group. The effect size (Effect Size) of the two groups is 0.8, α=0.05, Power=0.9, and this means that the sample size for the treatment group is 52 cases, and the sample size for the health group is 26 cases; taking into account variables like fewer visits, an increase in cases, and an increase in cases. The sample size for the treatment group was 52 cases, and the sample size for the healthy group was 26 instances. After taking lost visitation into account, the sample size was expanded by 15%, resulting in 66 cases for the treatment group and 33 cases for the healthy group in this experiment.

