#### Assessment time point

2.8.3

The insomnia group will have the above information completed at enrollment and after 12 treatments, the scale will be collected again at 3 months follow up, and the health group will have serum collected only at the first enrollment.

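### The metabolite–PSQI Spearman correlation takes in 3-month PSQI although serum stops at end of treatment; neither the visit pairing nor the handling of repeated values is defined, and correlating levels does not test whether changes go together

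*Protocol article*

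**What the plan says.** The visit schedule is consistent throughout the protocol article.

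- **Serum, insomnia group.** The abstract's Methods paragraph gives two time points: "serum will be collected at baseline, at the end of treatment". Section 2.1 (Study design) agrees that the last sample is the one at end of treatment.
- **PSQI and the other scales.** The same abstract paragraph gives three: "the scale will be collected at baseline, after 4 weeks of treatment, and at 3 months of follow-up". Section 2.8.3 (Assessment time point) repeats the third visit and mentions only questionnaires there: "the scale will be collected again at 3 months follow up".
- **The correlation.** Section 2.9.3.2.4 (Multivariate statistical analysis) ends by comparing the relative serum content of the screened markers with "PSQI scale scores, including follow-up data", and says that Spearman's "rank correlation analysis was carried out for each metabolic marker".

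That section names no visit pairs, lag, change score, visit-wise split or repeated-measures method. It does not say that visits are combined.

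**The concern.** Two things are at stake.

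**Pairing and repeated values.** The article brings follow-up PSQI into an analysis for which its own schedule provides no follow-up serum. A 3-month score can enter only against an earlier serum value (baseline, end of treatment, or the change between them), and these answer different questions. If all visits go into one correlation per marker, each patient contributes two or three rows. The ordinary Spearman test treats those rows as independent.

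**The question answered.** PSQI and metabolomics are both primary outcomes, and the Discussion wants to attribute symptom improvement to regulation of metabolic pathways. All insomnia patients receive the same electroacupuncture, so there is no untreated insomnia group to separate treatment from time. The informative patient-level question is whether those whose metabolites move are those who sleep better. A correlation of levels mixes stable differences between patients with any trend common to all of them, and does not address that question even when each visit is analysed alone.

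**Working it through.** The article gives no sample size, power or error rate for this correlation, so there is no figure to reproduce.

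**Inputs from the article**
- Serum visits: 2. PSQI visits: 3.
- Patients: section 2.3 plans "66 cases for the treatment group and 33 cases for the healthy group". All 66 patients might enter, or about 33 if only Group A (the untargeted platform) supplies relative content. Both were tried.
- PSQI shift: section 2.3 anticipates a fall of 2.63 points with an SD of 3.32, so 2.63/3.32 = 0.79, or about 0.8 SD. It is used here only as a plausible scale.
- Test level: 0.05 two-sided, borrowed from the univariate screen in the same section, because none is given for the correlation.

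**Assumptions, not in the article**
- Within-person correlation r of metabolite and of PSQI: 0.3, 0.5, 0.7.
- Metabolite shift over treatment: 0, 0.5 or 0.8 SD.

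**Simulation.** Metabolite and PSQI were generated as unrelated, both between and within patients (3,000 or 5,000 runs per setting). Three-row pooling re-uses end-of-treatment serum for the 3-month PSQI. The entries are the percentage of tests with p < 0.05; ranges cover repeat runs and 33 or 66 patients.

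| Setting | Rows per patient | r = 0.3 | r = 0.5 | r = 0.7 |
|---|---|---|---|---|
| No time shifts | 2 | 6.1–6.6 | 7.5–8.3 | 10.6–11.5 |
| No time shifts | 3 | 8.8–9.0 | 13.0–13.1 | 17.0–17.3 |
| PSQI falls about 0.8 SD, metabolite shifts 0.5 SD | 2 | 11.1–17.1 | 11.8–19.1 | 14.4–21.3 |
| PSQI falls about 0.8 SD, metabolite shifts 0.5 SD | 3 | 15.7–21.6 | 17.8–24.5 | 21.8–28.2 |
| PSQI falls 0.8 SD, metabolite does not shift | 2 | 5.0–5.4 | 6.1–6.5 | 8.0–8.1 |
| PSQI falls 0.8 SD, metabolite does not shift | 3 | 7.8–8.7 | 10.8–11.2 | 15.0–16.6 |

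With a 0.8 SD metabolite shift the rates are 19%–37% (two rows) and 25%–44% (three rows).

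One row per patient (baseline with baseline, change with change, or end-of-treatment serum with 3-month PSQI) gives 4.3%–5.6% in every setting. The Monte Carlo standard error at 5% is √(0.05 × 0.95/5000) = 0.3 points, so this is nominal.

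**Check by formula, no shifts.** Repeated rows multiply the null variance of the correlation by about V, and the rejection rate becomes 2[1 − Φ(1.96/√V)].
- Two rows: V = 1 + r². For r = 0.3, 0.5, 0.7, V = 1.09, 1.25, 1.49, giving 6.1%, 8.0%, 10.8%.
- Three rows, with one serum value used twice: V = 1 + (2/3)(2r² + r). V = 1.32, 1.67, 2.12, giving 8.8%, 12.9%, 17.8%.

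Both agree with the simulation. V does not contain the number of patients, so a larger sample does not remove this inflation.

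**Why joint shifts add to it.** With two pooled visits, a PSQI fall of 0.8 SD and a metabolite rise of 0.5 SD create a covariance of −0.25 × 0.8 × 0.5 = −0.10. The variances become 1 + 0.25 × 0.64 = 1.16 and 1 + 0.25 × 0.25 = 1.0625. The resulting (product-moment) correlation is −0.10/√(1.16 × 1.0625) = −0.09, with no link within any patient. This is a bias, so the rejection rate grows with sample size; that is why the upper ends of the 0.5 SD rows come from 66 patients.

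**The case against.** The strongest reply is that the text does not describe pooling. A separate Spearman correlation at each PSQI visit fits the sentence too, has one row per patient and keeps the nominal error rate. That stands: a reader might infer that the plan counts each patient two or three times, but the article does not say so, and the inflated rates cannot be presented as a property of the stated analysis.

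A reader might also infer that using 3-month PSQI without 3-month serum is itself an error. It is not. Relating earlier serum to later PSQI is a legitimate lagged analysis if it is declared, and it held 5% in the check above.

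It can further be said that visit pairing is detail a journal article leaves to the full protocol or analysis plan. This has some force for the handling of repeated values. It has less for the rest: the article itself brings follow-up scores into the analysis and specifies levels as the quantity correlated, and a clearer analysis of levels would still not answer the change question.

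Two limits on the numbers also stand. The 0.79 SD comes from a sample size paragraph that treats it as a difference between groups, with a drug control group supplying the mean and SD, so it is not clearly a within-patient change. And the correlation is not the only stated route from metabolites to benefit: the Discussion also plans a before–after comparison to see whether abnormal metabolites are reversed. The correlation is the only analysis described that relates the two outcomes patient by patient.

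**Conclusion.** The point holds in a limited form. It is established from the text that follow-up PSQI enters the correlation, that no serum is taken at that visit, and that the pairing and the treatment of repeated values are undefined. It also holds, whichever way visits are handled, that correlating levels does not show whether patients whose metabolites change are those who improve.

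The false-positive figures are conditional on pooling, which is a natural reading but not a stated one, and on the assumed within-person correlations and metabolite shift. Under pooling they span about 6%–17% without shifts and about 11%–28% with the 0.8 and 0.5 SD shifts. They are close to nominal (about 5%–8%) for two-visit pooling when the metabolite does not move. Markers that do move with treatment are, however, the ones the trial is looking for.

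This should be corrected before analysis. It does not affect the conduct of the trial.

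**What to change.** Reword the last sentence of section 2.9.3.2.4 so that every correlation uses one row per patient and names its visits:

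1. **Main association:** Spearman correlation of metabolite change (week 4 minus baseline) with PSQI change over the same interval.
2. **Month 3, separately and labelled as lagged:** week-4 metabolite change (from baseline) against PSQI change from baseline to month 3.
3. If visits are to be combined in one analysis, name a repeated-measures method instead of the ordinary Spearman test.

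Benjamini–Hochberg control over the markers tested would be a reasonable addition, but it addresses multiplicity and is separate from the visit-pairing problem.

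The cost is analysis wording only: no extra visits, samples or patients. The article reports that recruitment is still under way, so the change can be made before any analysis.
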